### Procedure

In *Austria,* HPs will register online and complete an online questionnaire including the consent to the study as well as questions about their professional background. After registration, they will be randomized to one of the study arms (I-PREGNO combined with TAU versus TAU only). Afterwards the study coordinator will get in contact with the HPs via telephone (onboarding). During the telephone call, the HPs will be informed about the condition they have been randomly assigned to and will receive a 20-30 minute briefing with instructions on the study materials. Before they start the recruitment of families, HPs who have been assigned to the intervention condition will receive a five-hour-online-training for the blended counseling. In a second step, the HPs will start to inform every pregnant woman, who has an appointment for the first counseling (between week 18-22 of pregnancy), and send the registration link to interested families. Interested families will also receive information material and data protection information. After the registration, families that meet the eligibility criteria will receive a link for the online baseline questionnaire (t0) from the study team, which has to be completed before the appointment with their midwife. After the families have completed the baseline assessment, the HP and participants receive a message to start the intervention phase and, in case of the intervention condition, a download guide for the app. Five weeks before birth, families receive the link for a second assessment (t0.5) via email. Eight weeks after birth, the families will receive the link for the post assessment (t1), which marks the end of the intervention. Three months after the end of the intervention, participants will be asked to complete a follow-up online questionnaire (t2). In case of non-response, participants will be reminded via email and telephone through the I-PREGNO coordination team.

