### Outcomes

Our primary outcome will be body composition measured through body mass index (BMI) of the family members (self-reported, the mother’s, if available father’s and the child’s height and weight). Secondary outcomes will be eating behavior (i.e., eating styles), physical activity, and psychological factors (i.e., depression, emotion regulation, parental stress) that are associated with the family’s well-being and influence eating behavior and physical activity. Information about the children (height, weight, breastfeeding) is collected through the mothers. Since the project primarily intends to reach psychosocially burdened families another focus lies on socio-demographic characteristics and socio-economic stressors (e.g., whether families receive social support, health status, crowded living conditions, and the migrant status of the parents). Data will be gathered at three (Germany) or four (Austria) time points. Tables 2 and 3 provide an overview of the included measurements.

**Table 2 Tab2:** Data collection at different time points during the study in Austria

Questionnaire	t_0_	t_0.5_	t_1_	t_2_
	18^th^ to 22^nd^ week of pregnancy	35^th^ -37^th^ week of pregnancy	8 weeks pp	3 months after t_1_
Socio-demographics	x			
Weight of the parent	x	x	x	x
Child’s weight and height			x	x
DEBQ	x	x	x	x
FFQ	x	x	x	x
IPAQ	x	x	x	x
EPDS	x	x	x	x
DERS-SF	x	x	x	x
ECR-RD		x		
GSE	x	x	x	x
CTS		x		
PSI-SF			x	x
PBQ			x	
I-FEEL				x
Regulatory Disorders				x
MAUQ			x	

*DEBQ* Dutch Eating Behaviour Questionnaire, *FFQ* Food Frequency Questionnaire, *IPAQ* International Physical Activity Questionnaire, *EPDS* Edinburgh-Postnatal-Depression-Scale, *DERS-SF* Difficulties in Emotion Regulation Scale, *ECR-RD* Experiences in Close Relationships, *GSE* General Self-Efficacy Scale, *CTS* Childhood Trauma Screener, *PSI-SF* Parenting Stress Index, *PBQ* Postpartum Bonding Questionnaire, *MAUQ* mHealth app usability questionnaire, *pp* postpartum

**Table 3 Tab3:** Data collection at different time points during the study in Germany

Questionnaire	t_0_	t_1_	t_2_
	0-12 months pp	3-15 months pp	3 months after t1
Socio-demographics	x		
Weight of the parent	x	x	x
Child’s weight and height	x	x	x
DEBQ	x	x	x
FFQ	x	x	x
IPAQ	x	x	x
EPDS	x	x	x
DERS-SF	x	x	x
ECR-RD		x	
GSE	x	x	x
CTS	x		
PSI-SF	x	x	x
PBQ	x	x	x
I-FEEL			x
Regulatory Disorders			x
MAUQ		x	

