#### Experiences in close relationships

To assess partnership quality, the German version of the Experiences in Close Relationships-Revised (ECR-R) questionnaire will be used [60]. It is a 9-item short version to assess attachment anxiety and avoidance in adult partnerships. Participants rate statements concerning their partnership on a 7-point Likert scale ranging from 1 (‘strongly disagree’) to 7 (‘strongly agree’). Overall, the ECR-R has good psychometric properties [60].

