#### Parent-Child interaction

Parent-child interaction will be assessed by the German version of the Postpartum Bonding Questionnaire [70]. Originally, the questionnaire was developed as a screening instrument in order to diagnose bonding disorders consisting of 25 items yielding scores on four factors [71]. The German version consists of 16 items. The response categories range from 0 (‘always’) to 5 (‘never’) on a 6-point Likert scale with a higher sum score indicating impaired bonding. The sum scores range between 0 and 80 points. Reck et al. [70] report satisfying psychometric properties.

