#### App usage

The quantitative (i.e., login, logout times, sessions and modules completed, time spent in the app) and qualitative (i.e., participants input, used features, content utilized) app usage and engagement will be assessed by the apps’ meta-data log files. The fundamental data are internally tracked within the app and downloaded to secure servers. Treatment adherence will be operationalized as time spent using the app, numbers of days using the app and worked-through sessions and modules. If variance of data allows for it, we will define user patterns (e.g., heavy vs. minimal users) as outcome and mediator variables.

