### Data collection and management

Data will be collected through three (Germany) or four (Austria) online assessments. Participating mothers and fathers complete the questionnaires separately, so that we will receive at least one questionnaire per family (from the mother) for every time point. Links to the assessments are sent out to the families at the corresponding time points (see the description of the procedure above for more details). The questionnaires should ideally be completed in the days after the family receives the link and not later than one month after that. If this period is exceeded at t1, participants will be excluded from this measurement point, but will still receive invitations to later time points. Furthermore, there will be two short online surveys for the HPs gathering information about their professional background and the families’ exclusion and inclusion criteria. We will also collect app-usage data from participants of the intervention arm. The data will be kept in accordance with the data protection guidelines of the European Union. Contact details will be maintained separately from questionnaire data. The collected data will only be marked with the individual study codes. The list with codes will be kept separately and is password protected.

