### Statistical analyses

In multilevel analyses, we will assess whether the clustered nature of the data (individuals clustered within families and HPs) has an effect on the results. If present, the impact of the intervention on the primary outcome and secondary outcomes will be analyzed using multi-level-models. If not, linear regression analysis will be used. Analyses of intervention effects will be based on the intention-to-treat principle. Given the cluster randomized design of the study, analyses on intervention effects will be adjusted for baseline values of the outcome. If suitable, missing data will be checked for randomness and be imputed using multiple imputations. Furthermore, we plan to assess the influence of moderating (stressful life events, parent child interaction, social support, partnership quality) and mediating (emotion regulation, self-efficacy) variables to identify determinants and pathways for the intervention’s efficacy and unhealthy weight gain during pregnancy and postpartum.

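### Partnership quality (both trials) and bonding (Austria) are planned as moderators but first measured after the intervention starts, and app use, logged in one arm only, is named as a possible mediator

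*Protocol article*

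**What the plan says.** The Statistical analyses section of the protocol article says "we plan to assess the influence of moderating (stressful life events, parent child interaction, social support, partnership quality" and goes on to name "mediating (emotion regulation, self-efficacy) variables to identify determinants and pathways for the intervention’s efficacy".

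Two of the four moderators are tied to instruments elsewhere in Methods: "To assess partnership quality, the German version of the Experiences in Close Relationships-Revised (ECR-R) questionnaire will be used", and "Parent-child interaction will be assessed by the German version of the Postpartum Bonding Questionnaire". Their timing is fixed in Table 2 (Austria) and Table 3, "Data collection at different time points during the study in Germany".

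Under Procedure, the intervention phase in both trials opens once the baseline questionnaire is completed. For Austria the section adds that "the families will receive the link for the post assessment (t1), which marks the end of the intervention"; in Germany t1 follows after 12 weeks.

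On app use, the App usage section says that, if the data vary enough, "we will define user patterns (e.g., heavy vs. minimal users) as outcome and mediator variables". Data collection and management says "We will also collect app-usage data from participants of the intervention arm". Under Procedure, control families get the app only after t2.

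**The concern.** A moderator analysis asks whether the treatment effect differs between kinds of family, where the kind is fixed before treatment can act. If the moderator is measured later and the arm can move it, families with the same score in the two arms are no longer the same kind of family. The interaction then mixes effect modification with the effect of treatment on the moderator.

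That is plausible here. One app module addresses social competences and social support, fathers have their own app version, and the Background argues that involving fathers eases stress in the family. Partnership and bonding scores could respond to any of these.

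App use raises a different problem. It has no counterpart in controls, and families choose how much to use the app, so a gradient with use may reflect motivation.

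At stake is the stated aim of identifying determinants and pathways of efficacy. The timing of a questionnaire cannot be left to a later analysis plan: a baseline that was not collected cannot be recovered.

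**Working it through.** **Step 1. Planned role against schedule.** Roles come from Statistical analyses and App usage, times from Tables 2 and 3.

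| Variable | Planned role | Austria | Germany | t0 value? |
|---|---|---|---|---|
| Partnership quality (ECR-RD) | moderator | t0.5 | t1 | neither trial |
| Parent-child interaction (PBQ) | moderator | t1 | t0, t1, t2 | Germany only |
| Emotion regulation (DERS-SF) | mediator | t0, t0.5, t1, t2 | t0, t1, t2 | both |
| Self-efficacy (GSE) | mediator | t0, t0.5, t1, t2 | t0, t1, t2 | both |
| App-use patterns | possible mediator | log files, intervention arm | log files, intervention arm | not applicable |

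The intervention starts after t0, so t0 is the only measurement before it. A planned moderator lacks that value in 2 of 2 trials for partnership quality and 1 of 2 for bonding. A mediator named in Statistical analyses lacks it in 0 of 2.

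**Step 2. Can a late moderator mislead?** The plan gives no figure to reproduce, so this is an illustration with assumed values:
- Baseline trait U has mean 0 and variance 1. Outcome Y = −0.45·A + 0.5·U + error (SD 0.87), where A is 1 in the intervention arm. There is no true interaction. The variance of Y is 0.25 + 0.757 = 1.007, so units are close to outcome SDs.
- The measured moderator in controls is M = U + noise (SD 0.5). In the intervention arm it is M = (1 − k)·U + 0.3 + noise (SD 0.5): shifted by 0.3 and compressed by k.

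The slope of Y on M within an arm is 0.5·(1 − k) / [(1 − k)² + 0.25], with k = 0 in controls.
- Controls: 0.5 / 1.25 = 0.400.
- Intervention, k = 0.3: 0.35 / 0.74 = 0.473. Spurious interaction 0.473 − 0.400 = 0.073.
- Intervention, k = 0.6: 0.20 / 0.41 = 0.488. Spurious interaction 0.088.

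The fitted arm effect at M = 0 is −0.45 − 0.3 × slope: −0.592 for k = 0.3 and −0.596 for k = 0.6, against a true −0.45. A simulation of 400,000 records gave interactions of 0.074 and 0.094 and arm effects of −0.592 and −0.598. With no shift and no compression it returned 0.00 and −0.45.

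A pure shift of 0.3 (k = 0) leaves the interaction at zero but still moves the arm effect at M = 0 to −0.45 − 0.3 × 0.400 = −0.57. Spurious moderation therefore needs more than a uniform shift.

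**Step 3. Scale against sampling error.** The planned 100 families per arm with 20% dropout leave 80. The residual variance in each arm is 1.007 − slope² × Var(M): 0.807 in controls, 0.841 (k = 0.3) and 0.909 (k = 0.6) in the intervention arm. The standard error of the interaction is √[0.807/(80 × 1.25) + 0.841/(80 × 0.74)] = 0.149 for k = 0.3, and √[0.807/(80 × 1.25) + 0.909/(80 × 0.41)] = 0.189 for k = 0.6. The distortion is about half a standard error in one trial, and it does not shrink with more families.

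**Step 4. App use.** Controls have no app before t2, so their app use is absent by design. In the intervention arm it varies, and the Interventions section lets users work through modules as they like. A mediator analysis needs exposure–mediator and mediator–outcome relations estimated across arms; here only a within-arm, self-selected association is available.

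**The case against.** The strongest reply is that the defect is limited. The named mediators have baseline and repeated values in both arms, German PBQ has a baseline, and whether families receive social support is listed with characteristics that appear to be collected at t0. The childhood maltreatment screener is retrospective, though the article does not say that it is the measure of stressful life events. The article lists moderators for both trials together, so bonding might have been meant as a moderator in Germany only. All of this stands, and it confines the point to partnership quality, Austrian bonding and app use. It does not rescue ECR-RD, which has no baseline anywhere.

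Four stronger readings are tempting and are not supported:
- A reader might infer that the moderator and mediator analyses as a whole cannot show who benefits or why. Emotion regulation or self-efficacy at t0.5 or t1 can precede an outcome at t1 or t2, subject to the usual no-confounding assumptions.
- A reader might infer that app use merely duplicates the arm. It varies among intervention families; the limitation is self-selection and the absence of a control counterpart.
- A reader might infer that a complier-average effect with allocation as instrument solves the app-use problem. Allocation also brings counselling by trained healthcare professionals, so it does not act through the app alone, and counselling effects would be credited to the app.
- A reader might size the problem by the share of families that an assumed shift moves across a median. The plan proposes no median split, and such a share is not a bias in an interaction.

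Also fair: t0 is before the intervention but not before allocation, because professionals are randomised first and families learn the arm during recruitment. A t0 value removes the effect of the intervention on the moderator, not any difference in who is recruited.

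**Conclusion.** The point holds for three items. Partnership quality in both trials and bonding in Austria are measured only after the intervention has begun, so their arm-by-moderator terms do not describe effect modification by how families were beforehand. App-use patterns cannot serve as a between-arm mediator.

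The timing follows directly from the tables and needs no assumption. That the intervention actually changes these scores is plausible from its content but not shown. The 0.07 to 0.09 interaction is an illustration under assumed values, smaller than its sampling error in one trial, so the main harm is to interpretation.

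Missing data add a little. In Germany t1 is the only ECR-RD occasion, and a family that answers more than a month late is excluded from t1 but still invited to t2, so it can have a t2 outcome and no moderator value. The documents do not say how many. The 20% dropout allowance should not be read as that number, because families lost altogether usually lack the later outcome too.

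These are supplementary analyses; the primary comparison is not affected.

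**What to change.** - Give the 9-item ECR-RD at t0 in both trials to families not yet past t0, and restrict its moderator analysis to families with a t0 value.
- State that only t0 values are used as moderators. For parent-child interaction this means PBQ at t0 in Germany.
- In Austria, where t0 precedes birth and no baseline bonding score is possible, treat PBQ as an outcome, not a moderator.
- In App usage, remove the mediator role. Report use patterns descriptively within the intervention arm, without a complier-average analysis that takes allocation as the instrument.
- Keep emotion regulation and self-efficacy as mediators, with the mediator measured before the outcome it is meant to explain.

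The cost is nine more items in the t0 questionnaire and some rewording. If recruitment has begun, the partnership moderator analysis will have a smaller sample, because families already past t0 cannot contribute a baseline value.

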## Discussion

The transition to parenthood represents a crucial phase for the development of psychosocial stress and overweight in parents and their offspring. Families with high psychosocial burden are considered as a vulnerable group who are often not reached through existing preventive measures [22]. Therefore, I-PREGNO with its focus on this group fills an important gap. Perinatal mHealth interventions have the potential to overcome this problem and provide a low cost and low threshold intervention that promotes the mental and physical health of psychosocially burdened families. In this research project, we developed a blended counseling intervention named I-PREGNO that combines a face-to-face counseling program with a self-guided app. I-PREGNO consists of a comprehensive prevention strategy that addresses psychological transdiagnostic mechanisms underlying not only unhealthy weight gain, but also a wider range of mental health problems. The intervention supports families throughout the complete perinatal period and provides specialized content for both pregnancy and the postnatal period. In addition, we use a family-based approach, which means that we have created a version for mothers and a version for fathers, addressing the needs of both parents separately. During the developmental phase of the intervention, we used an iterative user-centered design with a participative approach to increase the ease of use and the fit to the future user’s needs (i.e., psychosocially burdened families). Furthermore, we collaborated with HP of a German *Early Childhood Intervention* program to facilitate the implementation of our intervention in the current care structures. Furthermore, the results of the present study will not only provide further evidence for the efficacy of mhealth-based interventions, but will also contribute information about a vulnerable and neglected group, psychosocially burdened families, and provide more information about their burdens, risk and protective factors, needs, and acceptance of preventive interventions.

While there are already many smartphone-based interventions for pregnancy and the postpartum period, I-PREGNO is the first mHealth intervention that targets psychosocially burdened families. With the present study, we aim to examine the efficacy of I-PREGNO on unhealthy weight gain and families’ psychosocial stress within a large, multinational cRCT of vulnerable families during pregnancy and the postpartum period. A major challenge of our study will be to reach the calculated sample size, as the target group is difficult to reach. In order to minimize recruitment problems, we established contacts with coordinators of institutions and HPs throughout Germany and Austria who have experience with the target group and who will consult us during the recruitment. We plan to recruit mothers and fathers and aim to generate more evidence for the efficacy of smartphone-based interventions and to gain more knowledge about the acceptance of digital interventions within psychosocially burdened samples. As we are already in contact with stakeholders and policy institutions, our intervention could easily be translated in other languages and transferred to public health policy.

## Data Availability

Not applicable.

## Abbreviations

BMI: Body Mass Index
cRCT: Cluster randomized controlled trial
CTS: Childhood Trauma Screener
DEBQ: Dutch Eating Behaviour Questionnaire
DERS-SF: Difficulties in Emotion Regulation Scale
ECR-RD: Experiences in Close Relationships
EPDS: Edinburgh-Postnatal-Depression-Scale
FFQ: Food Frequency Questionnaire
GSE: General Self-Efficacy Scale
HP: Healthcare professional(s)
IPAQ: International Physical Activity Questionnaire
MAUQ: mHealth app usability questionnaire
mHealth: Mobile health
PBQ: Postpartum Bonding Questionnaire
PSI-SF: Parenting Stress Index
SES: Socioeconomic status
TAU: Treatment as ususal
